### Outcomes

#### Primary outcome

Change of ASD-specific symptoms is of strong clinical relevance due to long-term effects on adult outcome of the disorder [8, 23]. Therefore, the absolute change of ASD-specific symptoms, measured by the average total score of the Brief Observation of Social Communication Change (BOSCC-AT; latest version from 11 December 2017) between baseline (T2) and 1-year follow-up (T6) is the primary outcome measure. The BOSCC [24, 44, 48] is a new, reliable (inter-rater intraclass correlation coefficient (ICC) = .98), change-sensitive and valid observational measure to study change in social communication and interaction as well as repetitive and stereotyped behaviours in ASD which has been recommended in a recent Health Technology Assessment [42].

#### Other measures - diagnostic assessments

The *ADI-R* is a semi-structured diagnostic interview with the parents, assessing the core autism symptoms in the areas of social interaction, communication and stereotyped behaviour [49, 50].

The *ADOS-2* is an observational; semi-structured and standardised assessment of communication, social interaction, play and restricted and repetitive behaviours. It is the gold standard to use for ASD diagnosis [51–53]. It comprises different modules dependent on age and verbal level.

The *Bayley Scales of Infant and Toddler Development – Third Edition (Bayley-III)* [54] is an international developmental test und will be used for children with a developmental age below or equal to 42 months at the respective time point. The reliability for the German version lies between *r* = .77 and *r* = .89, and construct validity is comparable to the original version. In this study, the cognitive, language and fine-motor subscales will be used.

The *Wechsler Preschool and Primary Scale of Intelligence (WPPSI-III)* [55] is an international multidimensional measure of intelligence for preschool-aged children (3;0–7;2 years), and will be used in children with a developmental age > 42 months. Reliability is high with *r* = .95 for total IQ.

No valid, uniform IQ test covering the entire developmental age of the sample is available in Germany, thus the two different IQ measures with current norms had to be chosen.

#### Secondary outcomes

##### Child - ASD-specific symptoms

The *BOSCC subscales* (social communication BOSCC-SC, restrictive and repetitive behaviour BOSCC-RRB) and single items are examined for a differentiated picture of change in ASD-specific symptoms [24, 44]. Mean single-item scores have shown satisfying inter-rater reliability (ICC = .54–.97) and internal consistency (social communication subscale BOSCC-SC *α* = .83, repetitive behaviour subscale BOSCC-RRB *α* = .41) in a recent version. A revised and updated version of the BOSCC will be used for this study, which is expected to show even higher reliability.

The *ADOS-2 comparison and domain scores* will additionally be used. The comparison score allows the comparison between different time points, independent of the respective module. The ADOS-2 comparison score is based on the ADOS severity score. To compare the subscales Social Affect (SA) and Restricted and Repetitive Behaviours (RRB) calibrated domain scores will be used [56]. The ADOS-2 shows high inter-rater reliability for modules 1–3, with an ICC of .96 for the overall total. Internal consistence varies from *α* = 0.87 to *α* = 0.92 in the SA domain and from *α* = 0.51 to *α* = 0.66 in the RRB domain [51].

The parent- and kindergarten-teacher-rated *Social Responsiveness Scale (SRS)* [57] measures social responsiveness. The internal consistence is high (*α* = .93–.97), and the SRS has shown moderate validity compared to other ASD-specific measures. It has been recommended for use in ASD early intervention trials [42]. We will use the Social Responsiveness Scale – short version (SRS-16) 16-item short version which has been shown to have a high internal consistency and reliably measures change of ASD symptoms in one social-communication domain [58].

The parent- and kindergarten-teacher-rated *Repetitive Behaviour Scale-Revised (RBS-R)* [59] measures ASD-specific repetitive behaviours. These behaviours can substantially interfere with family activities and learning processes. Internal consistency for the subscales is satisfying ranging from *α* = .78 to *α* = .91 [59]. High correlations with the Child Behaviour Checklist (CBCL) and the ADI-R were found, and factor structure and reliability have been replicated for young children with ASD [60, 61]. The German translation and analysis of German norming data of the RSB-R has replicated the factor structure of the original publication (unpublished data, Frankfurt).

##### Child - Cognition and language

Depending on the child’s developmental level a standardised test with current German norms is used to assess cognition and language. Different forms of early intervention in ASD have been shown to improve cognitive and language development [11, 12, 27], which is of long-term relevance, because higher IQ and language level in childhood predicted adult outcomes [8]. The *Bayley-III* [54] or the *WPPSI-III* [55] will be used in relation to the child’s developmental stage (see above, ‘Diagnostic process’).

##### Child - Additional measures

The parent rating form *Child Behaviour Checklist 1½-5 (CBCL1½-5)* [62] and the *Teacher Report Form 1½-5 (C-TRF)* [63] are two of the most widely used valid and reliable measures in clinical research, dimensionally measuring social-emotional or behavioural problems [64]. The CBCL has been recommended as one of 12 most valid instruments assessing outcome in ASD early intervention trials [42].

The *Behaviour Rating Inventory of Executive Function-Preschool Version (BRIEF-P)* [65] is a rating scale assessing executive function (EF) in preschool children (2;0 to 6;11 years). Internal consistency varies from between *α* = .75 and *α* = .96 depending on rater/subscale. Inter-rater reliability for the total score is *r* = .56. Concurrent validity was shown for CBCL subscales. In preschool children with ASD, real-world EF impairments were observed, which were not related to ASD symptoms [66]. Given the relevance of EF problems for adult outcome, change in EF by early intervention is an important outcome [67].

##### Parents and family

The German adaptation of the *Parenting Sense of Competence Scale (PSOC/FSW)* [68] is chosen to measure parental self-efficacy. It has been developed and used in previous DFG projects (Zukunft Familie I, Ha1400/14–1-4). The revised questionnaire has been validated with young children (2.5 to 6.5 years) and shown satisfying internal consistency for mother and father assessments (*α* = .78/.79). Convergent validity with other measures of parental stress and competences has also been confirmed in the validation study [68]. The PSOC has been used in several ASD studies [42].

The *Depression Anxiety and Stress Scales – short form (DASS-21)* [69] is chosen to measure parental mental distress. Internal consistency is high, varying from *α* = .76 to *α* = .91. The validation study has shown good convergent validity to other measures of depression and anxiety (*r* = .59 to *r* = .86). Parental mental distress likely influences parent-child interaction, and may be changed by early intervention [70].

The *Family Quality of Life Survey-2006 ID/DD version (FQOLS-2006-ID/DD)* was developed for the main caregivers of persons with intellectual and developmental disabilities and has been translated into 20 languages, including German [71]. It covers nine domains, of which four are assessed here. A validation study reported high internal consistency (*α* = .85) and concurrent validity (*r* = .63) with another quality of life measure [72]. Improving family quality of life for families with an ASD-affected member is an important goal in autism intervention [73].

### Predictors and moderators

IQ/DQ, BOSCC-AT, gender, ADI-R and both parent‘s educational status will be investigated. The educational status will be classified according to the *International Standard Classification of Education (ISCED)* 2011.

An eye-tracking battery will be applied at T2, T4 and T6. This *eye-tracking battery* includes measures of sensory perception and visual orientating preferences. These tasks include: pupil adaption fixation stability (PAFS), smooth pursuit (SMT), visual oddball (VOT), visual search (VST), non-social versus social reward (NSRT), dynamic emotion expressing faces (DEEF), natural scenes (NST), biological motion visual preference (BMVP) and joint attention task (JAT).

*Spontaneous imitation* is assessed by automated-movement analysis via depth sensor cameras during video-based assessments (ESCS, BOSCC, DCMA, ADOS-2).

*Parental treatment attendance* will be documented weekly by therapists [74].

### Mediating mechanisms

The *Early Social Communication Scales (ESCS)* [75] is a standardised behavioural observation measure of non-verbal communication and social interaction skills that typically emerge in children with a developmental age of 8 to 30 months. For joint attention and social interaction, inter-rater reliability is > .8. The ESCS have been used as a change-sensitive outcome measure of early intervention trials [42, 76].

Bayley-III scales: see above. The cognitive and fine-motor scales will be studied as mediators.

The *Dyadic Communication Measure for Autism (DCMA)* [77] systematically rates quality of dyadic parent-child communication. Inter-rater reliability was ICC = .8 for parent synchrony and ICC = .59 for child initiations. The DCMA has shown good sensitivity to change, and parent synchrony mediated the child’s ASD-specific outcome in a large RCT on parent-mediated early intervention [14, 23, 28].

*Parental treatment adherence and competence* in employing techniques at home will be studied by the A-FFIP-adjusted *Parent Adherence to Treatment and Competence Scale (PATCS)*, which has been used in previous early intervention trials [78]. It is a self-report with four items related to adherence and two items to competence; all rated by a 5-point scale (low to high); Cronbach’s α = .82.

### Procedures

#### Blinding

As the RCT is a behavioural therapy intervention study, blinding of participants, therapists, parents and kindergarten teachers is not possible. To minimise observation and detection bias, blinded trained observers will collect data for all direct observation measures (BOSCC, play session, ESCS, cognition, language) especially for the primary endpoint (BOSCC-AT). The rating will be done by independent coders blind to treatment and randomisation status.

#### Randomisation

After written informed consent and baseline testing for eligibility, patients will be allocated by randomisation in a 1:1 manner to the interventions groups using a centralised, web-based tool (randomizer.at). Block randomisation will be performed for each centre and gender to achieve equal group sizes within these strata.

#### Data collection

All findings including clinical data will be documented anonymous in the subject’s medical record and in the CRF.

The BOSCC will be done by an independent local tester who plays with the child. The BOSCC scores will be rated from video by independent raters located in Frankfurt. BOSCC video data will be stored until about year-2 of data collection. Regular coding will then be done by three to four raters, trained to high inter-rater reliability. Every fifth video will be coded by all coders for measuring ongoing inter-rater reliability. The BOSCC is coded based on a 12-min, semi-standardised videotaped play situation. Two 6-min segments are watched twice while taking notes, and are coded immediately by a standardised scheme. Fifteen items are rated from 0 to 5 according to item-specific decision trees. Mean values from both segments are calculated for each item, and the summary scores are derived: BOSCC-AT (total score, items 1–13; (without item 9)), BOSCC-SC (items 1–8), BOSCC-RRB (items 10–13) and BOSCC single-item scores.

In each centre, every second therapy session of the first five patients and every fifth session of the following patients are videotaped for quality assurance.

#### Data management

The Institute of Medical Biometry and Informatics (IMBI) is responsible for the data management using a validated system. In order to ensure that the database reproduces the CRFs correctly, a double entry of data is performed by two different persons. A query process based on a beforehand-specified data-validation plan is established. Any entry and correction in the study database will be reported automatically in an audit file. All data management activities will be done according to the current Standard Operating Procedures (SOPs) of the IMBI.

### Statistical analysis

#### Sample size calculation

Sample size calculation refers to the primary outcome measure absolute change of BOSCC-AT between baseline (T2) and 1-year follow-up (T6). An age- and DQ-matched, but not randomised, observer-blind, case-control study of 2 x *N* = 20 children with ASD aged 3.2–7.9 years and an IQ/DQ of 37–134 at the start of intervention resulted in an A-FFIP 1-year effect size of 0.61 for the ADOS-severity score [27]. In a pre-post sample (*N* = 21) aged 3.8–5.8 years with a lower IQ/DQ 37–108, the 1-year pre-post effect size of the BOSCC-AT was 0.63 [24]. ADOS items are the basis for the ADOS-severity score and the BOSCC [48]. The BOSCC shows a higher number of items coded on a 6-point scale compared to the 2-point scale of the ADOS, resulting in higher variability capturing more subtle changes (range BOSCC-AT 0–60 versus range ADOS 1–10). For the BOSCC-AT, a more moderate, clinically meaningful, effect size of 0.55 is expected. With a significant level of *α* = 5% (two-sided) and a power of 1 − *β* = 80%, a sample size of 106 (2 × 53) is required to detect an effect size of 0.55 with the two-sample *t* test (ADDPLAN, version 6.1.1). Considering a drop-out rate of 20%, 134 (2 × 67) patients will be randomised to the treatment groups. It can be expected that including covariates in the confirmatory analysis will increase power compared to the *t* test.

#### Definition of analysis sets

Patients will be allocated to the different population sets (per-protocol set, full analysis set, according to the intention-to-treat (ITT) principle and safety set). A final definition of the analysis sets is in given the statistical analysis, which is finalised prior to the analysis.

#### Statistical methods

The primary analysis will be conducted based on the ITT population. Let *μ* denote the unknown true mean change of the BOSCC-AT between T2 and T6. The null hypotheses:

H_0_: *μ*_A-FFIP_ = *μ*_EIAU_ is tested against the alternative: H_1_: *μ*_A-FFIP_ ≠ *μ*_EIAU_.

The confirmatory test for treatment-group difference with respect to the primary efficacy endpoint will be done applying a mixed model for repeated measures (MMRM) approach [79] modelling the difference to baseline including the fixed-effects baseline BOSCC-AT, chronological age, treatment group, time, and treatment-group-by-time interaction; centre will be included as random effect. The time points of measurement are T2 (baseline), T4 (weeks 26–27) and T6 (weeks 52–54). The significance test for treatment-group difference will be based on least-squares means using a significant level of *α* = 5% (two-sided).

No missing data are expected for the covariates. Missing values for the primary outcome measure are dealt with as follows in the MMRM approach: The likelihood-based approach jointly models all actual observations without imputing missing data but using the within-patient correlation structure to provide information about the unobserved post-baseline primary outcomes and gives reliable results under the missing data at random (MAR) assumption. The MMRM approach shows favourable characteristics in terms of type-I error rate, power and bias of estimates as compared to alternative methods dealing with missing values, such as last-observation-carried-forward (LOCF) [79–81], even in the presence of a drop-out rate of 20% [82].

Data quality and homogeneity of intervention groups at baseline will be evaluated. All secondary endpoints will be analysed descriptively, using appropriate statistical methods.

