#### Exclusion criteria

Subjects presenting with any of the following criteria will not be included in the trial:
Non-verbal Developmental Quotient (DQ)/Intelligence Quotient (IQ) ≤ 30Non-verbal mental age ≤ 12 monthsDiagnosed vision or hearing impairments interfering with therapyCerebral palsyChronic neurological disorderUnstable epilepsyNeurodegenerative disorderRett/Angelman syndrome(History of) severe psychosocial deprivationInsufficient care by parentsAttachment disorderInstitutional upbringingParents not verbally fluent in German and/or unable to read German

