#### Additional analyses

As a sensitivity analysis the primary endpoint will be evaluated based on the per-protocol set of patients without major protocol violations. Additional sensitivity analyses will be done using LOCF and complete case analysis via analysis of covariance (ANCOVA) for repeated measurements. Safety analysis includes calculation and comparison of frequencies and rates of (S)AEs.

*Analysis of predictors and moderators*: in an exploratory fashion, implementing the above–mentioned MMRM approach, including the pre-specified variables as main or interaction effects in the respective models. For each pre-specified variable an own model will be calculated.

*Treatment mechanism* on the primary efficacy endpoint will be investigated following the mediation analysis approach described in Pickles et al. 2015 [28].

All analyses will be done using SAS® version 9.4, except for utilising Mplus software for the investigation of treatment mechanism.

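### The primary MMRM omits gender, a stratification factor, and baseline DQ/IQ; if either is prognostic, the analysis gives up a modest amount of precision

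*Protocol article*

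**What the plan says.** - **Allocation** (Protocol article, Randomisation): "Block randomisation will be performed for each centre and gender to achieve equal group sizes within these strata". Order of events: "After written informed consent and baseline testing for eligibility, patients will be allocated by randomisation in a 1:1 manner".
- **Confirmatory model** (Statistical methods): change from baseline in BOSCC-AT, "including the fixed-effects baseline BOSCC-AT, chronological age, treatment group, time, and treatment-group-by-time interaction; centre will be included as random effect". Neither gender nor DQ/IQ appears. The list is written out in full, so this is a stated choice and not a detail left for the SAP.
- **Availability of DQ/IQ** (Exclusion criteria): a non-verbal DQ/IQ of 30 or below excludes a child, so each randomised child needs a value beforehand. It comes from Bayley-III or WPPSI-III according to developmental age, because "the two different IQ measures with current norms had to be chosen" (Other measures - diagnostic assessments).
- **Planned use of both variables**: the list under Predictors and moderators opens with "IQ/DQ, BOSCC-AT, gender, ADI-R". Additional analyses makes this work exploratory: "For each pre-specified variable an own model will be calculated". The Background describes pre-treatment cognitive ability and sex only as possible predictors or moderators.
- **Power** (Sample size calculation): 106 evaluable children for a two-sample t test at an effect size of 0.55, inflated to 134. A power gain from covariates is expected there but not quantified.

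**The concern.** Two separate matters meet here.

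**Gender.** Stratified blocks force the arms to be balanced on gender. If gender predicts change in BOSCC-AT, that balance reduces the true variability of the treatment estimate. A model without gender leaves the gender variance in the residual, so its standard error does not reflect the reduction and the test is slightly conservative.

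**DQ/IQ.** This is not a stratum, so the argument is only one of efficiency: a baseline value already in hand could reduce residual variance. The Discussion names age, IQ and baseline ASD symptoms as the most frequently studied predictors or moderators. The model carries the first and third and leaves out IQ.

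What is at stake is precision. The validity of the primary test is not in question.

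**Working it through.** **1. The plan's own figure.** Inputs from Sample size calculation: d = 0.55, two-sided α = 0.05, 53 per arm, dropout 20%.

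Noncentrality = d·√(n/2) = 0.55·√26.5 = 2.831; df = 104; critical t = 1.983; power = 80.1% (52 per arm gives 79.3%). Dropout: 53/0.8 = 66.25, rounded up to 67 per arm, 134 in total. Both stated figures reproduce. The standard error in SD units is √(2/53) = 0.194.

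**2. Effect of the added terms.** Let R² be the share of residual variance that gender and DQ/IQ explain beyond the terms already in the model. The protocol gives no such figure, so a range is assumed. The standard error is multiplied by √(1 − R²) and the noncentrality divided by it.

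| Assumed R² | SE factor | SE change | Noncentrality | Power, 53 per arm | Equivalent children (106 × R²) |
|---|---|---|---|---|---|
| 0 | 1.000 | none | 2.831 | 80.1% | 0 |
| 0.02 | 0.990 | −1.0% | 2.860 | 80.9% | 2 |
| 0.05 | 0.975 | −2.5% | 2.905 | 82.1% | 5 |
| 0.10 | 0.949 | −5.1% | 2.984 | 84.1% | 11 |

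Charging two extra degrees of freedom changes these powers by less than 0.02 percentage points.

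**3. The starting point matters.** The 80.1% belongs to the unadjusted t test and not to the planned model. Suppose baseline BOSCC-AT and age already explained 20% of the variance (an assumption). The noncentrality is then 2.831/√0.80 = 3.165 and power 88.0%. A further 5% of the remainder gives 2.831/√(0.80 × 0.95) = 3.248 and 89.6%. The gain is 1.6 points, against 2.0 in the table.

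**4. Simulation check.** Settings: 106 children, four centres, 20% girls (from the 4:1 ratio in the Background), blocks of four within centre and gender, one complete endpoint, centre fitted as fixed effects, 6,000 runs per scenario, d = 0.55. It is a single-endpoint ANCOVA and not the full MMRM, so the figures are approximate.

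| Assumed R², gender / DQ | Mean SE: neither | Gender only | DQ only | Both | Power: neither → both |
|---|---|---|---|---|---|
| 0 / 0 | 0.1945 | 0.1946 | 0.1954 | 0.1956 | 80.4% → 80.1% |
| 0.01 / 0.05 | 0.1939 | 0.1930 | 0.1899 | 0.1890 | 80.0% → 81.7% |
| 0.02 / 0.10 | 0.1942 | 0.1923 | 0.1852 | 0.1832 | 80.4% → 84.8% |
| 0.05 / 0.20 | 0.1939 | 0.1890 | 0.1744 | 0.1689 | 80.4% → 89.6% |

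Gender alone lowers the reported SE by about 0.5% to 2.5%. In each scenario with a gain, DQ accounts for most of it, under R² values that were assumed larger for DQ.

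**5. Conservatism from omitting gender.** At a gender R² of 0.05 with no treatment effect, the model without gender or DQ reports a mean SE of 0.194. The estimate's actual SD is 0.190, close to 0.194·√0.95 = 0.189. Rejection is 4.3% without gender and 4.9% with it. The Monte Carlo error of each rate is √(0.05 × 0.95/6000) = 0.28 points, so the direction is informative but the second digit is not.

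**The case against.** The strongest reply is that nothing shows these variables to be prognostic. The Background calls them possible predictors only. The pilot described as "An age- and DQ-matched, but not randomised, observer-blind, case-control study" matched on DQ to make non-randomised groups comparable, which does not show that DQ predicts change in BOSCC-AT. Baseline BOSCC-AT and age are already in the model and may absorb much of what DQ/IQ would add. The planned 80% power does not rely on either variable. DQ/IQ also mixes two instruments, and separate exploratory models with gender and with IQ/DQ are already planned.

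Most of this stands, and it limits how strongly the point can be put. A reader might infer that the standard error is certainly larger than it need be, that DQ/IQ is an established prognostic factor, or that the trial is underpowered as it stands. The documents support none of these: they give no variance explained, and 80.1% is not the power of the planned model. A reader might also infer that a random centre effect with four centres is an error. It is an accepted choice, centre is in the model, and fixed against random is a trade-off.

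Two things remain. The exploratory models take one variable at a time and do not alter the confirmatory test. The two-instrument difficulty calls for a scoring rule, and the protocol already treats DQ/IQ as a single variable for eligibility and as a predictor.

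**Conclusion.** The point holds as a conditional one about efficiency. The confirmatory model does not carry one of the two randomisation strata, and it leaves out a baseline measure that every randomised child should have. There is no bias and no inflation of type I error.

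The size depends entirely on an R² that the protocol does not give. For an assumed 2% to 10%, the standard error falls by about 1% to 5% and power rises by 0.8 to 4.0 points from the t-test base, less if the planned covariates already raise power. If both variables explain nothing, the simulated standard error rises from 0.1945 to 0.1956, about 0.6%. The possible gain outweighs that loss, so the change is a cheap improvement worth making. It does not repair a defect in the test.

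**What to change.** Before unblinding, amend the primary MMRM in the protocol and SAP:

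1. Add gender as a fixed effect, so that both randomisation strata are represented.
2. Add baseline (T2) non-verbal DQ/IQ as a fixed-effect covariate beside baseline BOSCC-AT and age.
3. State how Bayley-III and WPPSI-III results are put on one scale, for example each expressed as its quotient, with an indicator for the test used.

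Fitting centre as fixed is optional; if it is adopted, the random-centre model can be kept as a sensitivity analysis.

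Cost: two degrees of freedom, or three with the test indicator, a short scoring rule and no new data. DQ/IQ would need to explain roughly 1% of residual variance to pay for itself. Gender, balanced by design, costs almost nothing.
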